## Abstract

**Background:**

The hamstrings are an important muscle group that contribute to horizontal force during sprint acceleration and are also the most injured muscle group in running-based sports. Given the significant time loss associated with hamstrings injury and impaired sprinting performance following return to sport, identifying exercises that drive adaptations that are both protective of strain injury and beneficial to sprint performance is important for the strength and conditioning professional. This paper describes the study protocol investigating the effects of a 6-week training program using either the hip-dominant Romanian deadlift (RDL) or the knee-dominant Nordic hamstring exercise (NHE) on hamstring strain injury risk factors and sprint performance.

**Methods:**

A permuted block randomized (1:1 allocation) intervention trial will be conducted involving young, physically-active men and women. A target sample size of 32 will be recruited and enrolled participants will undergo baseline testing involving extended-field-of-view ultrasound imaging and shear wave elastography of the biceps femoris long head muscle, maximal hamstrings strength testing in both the RDL and NHE, and on-field sprint performance and biomechanics. Participants will complete the 6-week training intervention using either the RDL or NHE, according to group allocation. Baseline testing will be repeated at the end of the 6-week intervention followed by 2 weeks of detraining and a final testing session. The primary outcome will be regional changes in fascicle length with secondary outcomes including pennation angle, muscle cross sectional area, hamstring strength, and maximal sprint performance and biomechanics. An exploratory aim will determine changes in shear wave velocity.

**Discussion:**

Despite extensive research showing the benefits of the NHE on reducing hamstring strain injury risk, alternative exercises, such as the RDL, may offer similar or potentially even greater benefits. The findings of this study will aim to inform future researchers and practitioners investigating alternatives to the NHE, such as the RDL, in terms of their effectiveness in reducing rates of hamstring strain injury in larger scale prospective intervention studies.

**Trial Registration:**

The trial is prospectively registered on ClinicalTrials.gov (NCT05455346; July 15, 2022).

**Supplementary Information:**

The online version contains supplementary material available at 10.1186/s13102-023-00680-w.

## Background

The hamstrings muscles act to both extend the hip and flex the knee, which are particularly important movements during sprinting. The hamstrings are primary contributors to horizontal force production during both acceleration and maximal velocity phases of sprinting [1, 2] with their contribution to propulsion increasing substantially as an athlete nears maximum speed [3]. Due to the increased lengthening and high negative work done by the hamstrings during the swing phase of sprinting [4–6], the hamstrings are also highly susceptible to injury in running-based sports [7–9]. Considering the significant incidence and subsequent time loss of hamstring strain injuries (HSI) in sport [8–14], identifying exercises that emphasize adaptations that are both protective of strain injury and beneficial to sprint performance is important.

One exercise that has garnered a lot of attention as an effective component for HSI prevention is the Nordic hamstring exercise (NHE), which involves minimal equipment and has been integrated within injury prevention programs, such as the FIFA11+ [15, 16]. The high eccentric demand placed on the hamstrings during the exercise [17] is a potent stimulus for inducing beneficial adaptations thought to be protective of HSI. These adaptations include increased fascicle length with concurrent decreases in pennation angle, muscle hypertrophy, and increased eccentric knee flexor strength [18–21]. Additional ultrasound-derived shear wave speed (SWS)—a proxy for muscle material properties and stiffness—may also contribute to injury resiliency [22], though chronic adaptations following eccentric training have not been consistently established [23].

Studies using both surface electromyography (sEMG) and magnetic resonance imaging have shown the NHE preferentially recruits the semitendinosus compared to the biceps femoris—the latter of which is the more frequently injured hamstrings muscle [17, 24, 25]. One possible explanation for the preferential recruitment of the semitendinosus is that the NHE is a knee-dominant exercise, whereas studies have shown the biceps femoris muscle is more active (proportionally to the semitendinosus muscle) in hip dominant exercises, such as the 45-degree hip extension and Romanian deadlift (RDL) [17, 24, 26–29].

The NHE loads the hamstrings at relatively short muscle lengths [30–33] compared to the RDL, the latter of which can be progressively loaded throughout a greater range of motion [34, 35]. Higher neuromuscular activation was also observed in the proximal region compared to the distal region of the biceps femoris muscle during the stiff-leg deadlift – a similar exercise to the RDL [36]. Together, the higher lateral to medial hamstrings muscular activation ratio and force generation throughout longer muscle lengths induced by the RDL may increase the potential to elicit potentially beneficial adaptations in the injury-susceptible biceps femoris muscle [1–6].

Compared to its injury prevention effects, the impact of the NHE on sprint performance is less clear [37–41]. The implications of the RDL as it relates to improving sprint performance also have not been well-described. Sprint performance is often defined by time, but this measure provides limited information into different aspects (e.g., sprint mechanics) or phases (e.g., acceleration, transition, maximal velocity) of a sprint. Kinematics are often assessed during maximal velocity sprinting and relate to both performance and hamstrings injury susceptibility [42, 43], suggesting the importance of assessing sprint performance with other metrics than just total or split times. Simple biomechanical methods (i.e., force-velocity profiling) have been described to assess sprint kinetics during a 60 m sprint [44]. These methods may be useful in differentiating between horizontal force and maximal velocity contributions to sprint performance [2, 44–47].

Considering the hamstrings’ contribution toward horizontal force production during sprinting, the anatomical determinants that may predispose the biceps femoris muscle toward force production, and the significant stretch the biceps femoris undergoes during swing phase [1, 2, 4, 48, 49], selecting exercises that target this muscle, particularly in an eccentrically-biased manner, could prove vital for muscular adaptations for both injury risk mitigation and sprint performance. Yet, it is unclear how eccentric training, particularly with RDLs, influences sprint performance. Additionally, architectural adaptations to training interventions should be investigated along the length of the muscle to determine if changes are more pronounced in different regions [48, 50] and if these correspond to regions more susceptible to strain injury [51], such as the proximal muscle-tendon junction of the biceps femoris [52, 53].

Therefore, the purpose of the study is to investigate the effects of a 6-week training program matching volume and eccentric contraction time between the RDL and the NHE on hamstrings architecture, hamstrings strength, and sprint performance. As an exploratory aim, ultrasound shear wave speed (SWS) will also be measured along the length of the muscle to determine chronic adaptations in tissue material properties following eccentric training. Findings from this study will aim to provide evidence for targeted exercise selection in addressing HSI risk factors with potential to inform rehabilitation programming.

## Methods/Design

### Overall study design

This study is a randomized intervention trial where participants will be allocated to one of two experimental groups: RDL or NHE training. The primary outcome of the study is the change in regional biceps femoris fascicle length between the two intervention groups. Secondary outcomes will include ultrasound-derived changes in pennation angle, muscle thickness, anatomical cross-sectional area, in addition to hamstrings strength, and maximal sprint performance. As an exploratory aim, we will determine changes in regional SWS following training and between the two intervention groups.

The study is registered on ClinicalTrials.gov (Identifier: NCT05455346) with all procedures approved by the Health Sciences Institutional Review Board at the University of Wisconsin-Madison. Written informed consent will be obtained from all participants before inclusion by study personnel with Human Subjects Protection training. Any changes in the protocol will be reflected on the clinical registration website of ClinicalTrials.gov.

An overview of the experimental design is given in Fig. 1. Inclusion criteria for participants eligible for the intervention trial are 18–25 years of age (consistent with previous investigations [29, 47, 54]), self-report of being physically active—as defined by the Physical Activity Guidelines for Americans [55],, having > 6 months experience in resistance training, no history of HSI within the last 6 months, no history of lower extremity surgery, no current musculoskeletal injury to the lower extremity, and females not currently pregnant. Physical activity will be defined as participating in weekly totals of 150–300 min (5 h) of moderate-intensity, or 75–150 min (2 h and 30 min) of vigorous-intensity aerobic physical activity, or an equivalent combination of moderate- and vigorous-intensity aerobic activity. Prior to the intervention, baseline assessments will be performed. These include regional ultrasound measures (see *Ultrasound Measures*); strength for the NHE and RDL (see *Nordic Hamstring Exercise and Romanian Deadlift Strength Testing*); and maximal 60 m sprints (see *Maximum Sprint Testing*). Each participant will also be asked to complete the Baecke questionnaire for determination of habitual physical activities and what current physical activities pertinent to the study in which they participate at baseline [56]. Participants will be able to continue usual levels and mode of physical activity but be asked to refrain from supplementary lower extremity resistance training and sprint-specific training.

**Fig. 1 Fig1:**
[figure not shown]
Proposed experimental design and outcome measures at each testing time-point

An *a priori* power calculation using R statistical software and “WebPower” package (wp.kanova function) [57] was performed. Using an effect size based the median Cohen’s d extracted from several relevant studies investigating the effects of NHE on the primary aim of fascicle length changes [19, 21, 26, 54, 58] and converting to Cohen’s f (f = 0.8), 2 experimental groups (RDL vs. NHE), a total of 12 factors (levels of intervention x time x imaging location (proximal, mid-belly, distal) = 2 × 2 × 3), α = 0.05, and power = 0.80, a total sample size of 11 participants per group will be required. This sample size is consistent with previous investigations of fascicle length following NHE training [19, 21, 26, 54, 58]. Using a conservative effect size (Cohen’s d = 0.5) based on observed 2% differences detected in sprint times between two eccentric training interventions (Cohen’s d = 0.87) [47] and converting to Cohen’s f (f = 0.25), a total sample size of 28 (N = 14 per group) will be required for the secondary aims. Based on the larger sample size and accounting for a 10% attrition rate, a total of 16 participants per group (N = 32 in total) will be recruited from the University of Wisconsin to participate. Participants will be compensated on a pro-rated basis for completing study visits and provided their strength and sprint results.

Participants will be allocated to either the RDL or NHE training group using a random permuted block randomization (1:1 training group allocation) using *a priori* computer-generated group numbers. Each participant will undergo the 6-week intervention program based upon their group allocation (see *Intervention*). A 6-week period was chosen due to previous observations that additional changes in fascicle length (primary outcome) were minimal with NHE training lasting > 6 weeks [47, 59] and is consistent with previous investigations of architectural changes induced by NHE [54, 58]. Following the 6-week intervention, participants will return to the lab for post-intervention assessments of regional ultrasound of the hamstrings, RDL and NHE strength testing, and sprint testing, which will be carried out in the same manner as baseline assessments. Fascicle length changes are known to return to baseline values within 2 weeks after the cessation of NHE [54, 60]. To investigate the potential short-term washout effects of the training intervention on the primary and secondary outcomes, participants will be asked to return to the lab following a 2-week detraining period. During these 2 weeks, participants will be encouraged to resume all normal activities but limit any outside eccentric hamstring strength training.

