## Discussion

Although much research has been dedicated to identifying the etiology and mechanisms of injury, potential risk factors, residual neuromuscular deficits, and evidence-based recommendations for rehabilitation protocols of HSI [4, 6, 10, 13, 18, 91–102], the incidence and injury burden of HSI have not improved [14, 103]. The NHE is a staple in injury prevention programs for HSI, but evidence suggests adherence is a major limitation in its effectiveness for reducing HSI [104–107]. Due to the high rate of injury within the proximal muscle-tendon junction of the biceps femoris and non-uniform muscular adaptation to resistance training, different exercises should be employed to target specific muscle regions and increase eccentric training adherence [52, 53, 108, 109]

Consistent eccentric hamstring strength training (specifically using the NHE) increases eccentric knee flexor strength and influences architectural adaptations thought to be protective of HSI—such as increased fascicle length with concurrent decreases in pennation angle [47, 50, 54, 59, 60, 97, 110]. Fascicle length, pennation angle, and muscle thickness are typically measured using ultrasonography at the mid-belly [2, 47, 54, 59, 60], but this does not account for the known variation in architecture along the length of the hamstrings muscles [48, 49, 111, 112] or the non-uniform lengthening, activation, and adaptations induced by resistance training [113–116]. Recent evidence indicated that changes in fascicle and sarcomere lengths only occur in the distal region of the biceps femoris muscle following NHE training [50]. This coincides with higher neuromuscular activation in the distal region compared to the proximal and middle regions of the biceps femoris muscle during the NHE [117]. Our proposed investigation aims to determine if hip-dominant (RDL) or knee-dominant (NHE) eccentric hamstring exercises influence regional differences in fascicle length adaptations

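### The primary power calculation uses the effect of NHE training as if it were the RDL-versus-NHE difference, so 80% power at 11 per group is not the power of the primary contrast

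*Protocol article*

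**What the plan says.** Under Overall study design the protocol article states: "The primary outcome of the study is the change in regional biceps femoris fascicle length between the two intervention groups". The sample size paragraph that follows Figure 1 takes the median Cohen's d from studies "investigating the effects of NHE on the primary aim of fascicle length changes". It then sets up the calculation by "converting to Cohen’s f (f = 0.8), 2 experimental groups (RDL vs. NHE") and "a total of 12 factors (levels of intervention x time x imaging location (proximal, mid-belly, distal) = 2 × 2 × 3"). With α = 0.05 and power 0.80 it concludes that "a total sample size of 11 participants per group will be required".

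For the secondary aims the same paragraph uses a different kind of input: a sprint-time difference observed between two eccentric training interventions (d = 0.87), reduced to d = 0.5 and converted to f = 0.25, giving 28 in total. The larger figure, with 10% attrition, sets enrolment at 32. The Abstract's Discussion says that alternatives such as the RDL "may offer similar or potentially even greater benefits".

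**The concern.** A power statement should rest on the size of the contrast to be tested. Here the contrast is RDL against NHE, two active exercises matched for repetitions and eccentric time, while the effect size describes what NHE training does to fascicle length. The protocol gives no RDL effect and no RDL-versus-NHE difference for this outcome, and its own rationale is that RDL may do about as well or better.

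At stake is how the primary result will be read. If the article claims 80% power and the difference is not significant, a reader may take that as evidence that the exercises are alike, when the interval would still allow sizeable differences either way.

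**Working it through.** **1. Reproduce the stated figure.** Inputs from the sample size paragraph: f = 0.8, 2 × 2 × 3 = 12 cells, α = 0.05, power 0.80, function wp.kanova. That function uses a noncentral F with λ = N f² and denominator df = N − number of cells.

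- N = 22, numerator df 2: λ = 22 × 0.64 = 14.08, denominator df = 10, power 0.826.
- N = 21: power 0.792. The smallest adequate N is therefore 22, or 11 per group, which matches.
- With 12 cells, numerator df of 1, 3, 5 and 11 give N = 18, 24, 29 and 38. Only 2 df gives 22.

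Two df fits group × time × region, (2−1)(2−1)(3−1) = 2. It also fits the region main effect and the two-way terms with region, and the paragraph does not name the term.

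**2. What f = 0.8 stands for.** The paragraph turns d = 0.5 into f = 0.25, so f = d/2 and f = 0.8 means d = 1.6. If the NHE gain is 1.6 SD and the RDL gain is r × 1.6 SD, the between-arm difference is |1 − r| × 1.6 SD. This equals 1.6 only at r = 0 or r = 2. At r = 0.5 it is 0.8, and at r = 0.75 it is 0.4. The protocol gives no r, so these are assumed values.

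**3. Power for a between-arm difference in change.** Two-sample noncentral t, n per arm, df = 2n − 2, noncentrality d√(n/2), two-sided 5%. Here d is in SDs of the change score, for one region, baseline to week 6.

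| Assumed d | n = 11 | n = 14 |
|---|---|---|
| 1.6 | 0.946 | 0.983 |
| 0.87 | 0.493 | 0.601 |
| 0.8 | 0.431 | 0.531 |
| 0.5 | 0.201 | 0.247 |
| 0.4 | 0.145 | 0.175 |

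The values 0.87 and 0.5 are the protocol's own between-intervention effects, but for sprint time; they serve only as reference points.

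**4. What the trial can detect.** Solving for 80% power gives d = 1.26 at 11 per arm and 1.10 at 14 per arm. The 95% CI half-width at 14 per arm is t(0.975, 26) × √(2/14) = 2.056 × 0.378 = 0.777 SD.

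**5. Independent cells versus repeated measures.** The calculation in step 1 treats the 12 cells as separate groups. The planned analysis is a mixed model with a participant random effect. To see what this does, take group × time × region with equal within-participant correlation ρ (assumed 0.5 to 0.8) and a difference of δ single-measurement SDs in one region only. Then λ = (n/2) × (2/3)δ² / [2(1 − ρ)], with 2 and 4(n − 1) df.

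- δ = 1.6: at n = 11, λ = 9.39 to 23.47 and power 0.76 to 0.99; at n = 14, power 0.86 to 0.999.
- δ = 0.8: at n = 11, power 0.24 to 0.54; at n = 14, 0.30 to 0.66.

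**The case against.** The strongest reply is that the 11 per group decides nothing. Enrolment follows the larger secondary figure, which does come from a comparison of two eccentric interventions and was deliberately reduced. That stands, and it is why no participants need adding and why this is not a critical fault.

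Three further points also stand in part.

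- A reader might infer that the plan assumes RDL has no effect at all. The documents do not support that. The article does not say whether the source d values are pre-post or against a comparator, and a difference of 1.6 SD could also arise if RDL did much better than NHE. What stands is narrower: no between-arm difference is given, and the figure used is described as an effect of NHE.
- A reader might infer that treating repeated cells as independent inflates the claimed power. Step 5 shows that it may be conservative. The Discussion cites evidence that "changes in fascicle and sarcomere lengths only occur in the distal region of the biceps femoris muscle following NHE training". If RDL produced no change and NHE gained 1.6 SD in one region only, the repeated-measures test would have power close to or above 80%. The independence assumption means that the stated 80% is not the power of the planned model; it does not mean that the true power is lower.
- Using two time levels although there are three test sessions is not an error. It fits the baseline to week 6 contrast, with the last visit serving to study washout.

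It can also be said that no equivalence claim is planned and that effect sizes will be calculated. That is true, and misreading a null result is a risk rather than a stated intention. None of this supplies the missing between-arm difference.

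**Conclusion.** The point holds and should be fixed. The 11 per group is correct arithmetic on an input that does not describe the primary contrast, and the calculation does not match the planned mixed model. The article therefore has no valid power statement for its primary question. With 14 completers per arm, a two-arm comparison of change in one region detects 1.10 SD with 80% power. Power is 0.531 if the true difference is 0.8 SD and 0.175 if it is 0.4 SD.

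These figures rest on assumed differences in change-score SDs, a single region, and no gain from modelling regions jointly. The SD unit of the source d is not stated, so reading 0.8 as half the NHE effect is an approximation. A reader might go further and conclude that the trial is too small or bound to be inconclusive. The documents do not support that, because they give no RDL-versus-NHE difference from which to judge it. Nor is it established that the three-way interaction was the term powered; it is only the most natural fit to 2 df.

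**What to change.** Replace the statement of 11 per group for 80% power with one for the primary contrast, for example:

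> With 14 completers per arm, a two-arm comparison of fascicle-length change from baseline to week 6 in a given region has 80% power for a difference of 1.10 SD of the change score; the 95% CI half-width is about 0.78 SD.

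Add one sentence: a non-significant difference will not be reported as similarity of RDL and NHE.

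N = 32 stays, and recruitment, procedures and analysis are unchanged. The cost is that the stated power looks less favourable than it does now.

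### The secondary-aim sample size of 28, which sets the enrolment target of 32, does not follow from the only power method named at f = 0.25; it matches an undescribed repeated-measures calculation for an effect about twice the one stated

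*Protocol article*

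**What the plan says.** All of this stands in the power-calculation paragraph of the protocol article (Methods/Design, Overall study design, after the Fig. 1 caption).

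- **Method.** R with the WebPower "package (wp.kanova function) [57] was performed". No other function is named.
- **Primary aim.** f = 0.8, two groups and "a total of 12 factors (levels of intervention x time x imaging location (proximal, mid-belly, distal) = 2 × 2 × 3"), leading to "α = 0.05, and power = 0.80, a total sample size of 11 participants per group will be required".
- **Secondary aims.** "Using a conservative effect size (Cohen’s d = 0.5"), scaled down from d = 0.87, which is attributed to "observed 2% differences detected in sprint times between two eccentric training interventions". This is converted to f = 0.25 and leads to "a total sample size of 28", 14 per group.
- **Enrolment.** The larger requirement is taken and 10% attrition added, giving 16 per group and 32 in total.

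For the secondary calculation the paragraph gives no numerator degrees of freedom, number of repeated measurements or within-person correlation, and it does not restate alpha or power. Elsewhere in Methods/Design, participants are tested at baseline, after six weeks and after two weeks of detraining. Outcome measures & statistical analysis plans linear mixed models with a random participant effect.

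**The concern.** The article states a method, an effect size and a result, so the result can be checked, and it does not follow. An effect of f = 0.25 is less than a third of the primary f = 0.8, yet the total rises only from 22 to 28. In a noncentral-F calculation the required N goes roughly with 1/f², so a much larger increase would be expected.

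The figure matters because it fixes enrolment and is the only support for the precision of the secondary comparisons. If it is taken at face value, a null difference between the Romanian deadlift and Nordic arms in a tested secondary outcome (pennation angle, cross-sectional area, muscle thickness, kinematics, force-velocity variables) could be read as coming from a comparison with 80% power for a half-SD effect.

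**Working it through.** **Inputs from the article:** f = 0.8 and 12 cells (primary); d = 0.5 and f = 0.25 (secondary); 1:1 allocation; 10% attrition.

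**Assumed:** alpha 0.05 and power 0.80, stated for the primary aim, carry over to the secondary aims. Numerator df is not stated, so 1 and 2 are both shown.

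**1. Reproduce the primary figure.** For wp.kanova (independent groups), power comes from a noncentral F with λ = N·f², df1 = numerator df, df2 = N − number of cells. With f = 0.8, 12 cells and df1 = 2 (the three-way interaction), N is 21.2, or 22 for two equal arms. That is the stated 11 per group, so the function is being applied as the article applied it.

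**2. Reproduce the attrition step.** 28/0.9 = 31.1, or 32 for equal arms. This agrees.

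**3. Same function at f = 0.25.**

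| Numerator df | N for 80% power | Power at N = 28 |
|---|---|---|
| 1 (2 to 12 cells) | 128 | 0.24–0.25 |
| 2 (2 to 12 cells) | 158 | 0.17–0.18 |

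At N = 28, λ = 28 × 0.0625 = 1.75; at N = 128 it is 8.0. The smallest f with 80% power at N = 28 is about 0.55. A two-sided two-sample t test at d = 0.5 agrees: 64 per arm, with power 0.25 at 14 per arm. Even the unreduced d = 0.87 has power of only 0.60 at 14 per arm.

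**4. Where 28 does come from.** For a repeated-measures group-by-time interaction with m measurements and correlation ρ, λ = N·m·f²/(1 − ρ), df1 = m − 1, df2 = (N − 2)(m − 1).

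- m = 3, ρ = 0.5: λ = 28 × 3 × 0.0625/0.5 = 10.5, power 0.812. At N = 26 power is 0.778, so 28 is exactly the answer.
- m = 2, ρ = 0.6: λ = 28 × 2 × 0.0625/0.4 = 8.75, power 0.813. Again 28.

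**5. What f = 0.25 means in that model.** The conversion f = d/2 holds for a two-group mean difference. For a group difference D (in raw SD) that appears at one follow-up, the interaction f is D/4 with two measurements and D/√18 with three. Setting f = 0.25 gives D = 1.0 or 0.25 × √18 = 1.06. Conversely, D = 0.5 gives f = 0.125 or 0.118.

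**6. Repeated-measures N for D = 0.5 raw SD.**

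| ρ | N for 80% power (m = 3 to m = 2) | Power at N = 28 (m = 2, m = 3) |
|---|---|---|
| 0.5 | 118–128 | 0.247, 0.245 |
| 0.8 | 48–54 | 0.522, 0.545 |
| 0.9 | 26–28 | 0.813, 0.853 |

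**7. Detectable difference with 14 completers per arm.** A two-sided t test on the change score reaches 80% power at 1.10 SD of the change score. The SD of change is √(2(1 − ρ)) raw SD, so in raw SD this is 1.10 × 1.00 = 1.10 at ρ = 0.5, 1.10 × 0.632 = 0.70 at ρ = 0.8, and 1.10 × 0.447 = 0.49 at ρ = 0.9.

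**The case against.** The strongest reply is that the trial measures participants repeatedly and plans mixed models, so a between-subject function is the wrong yardstick. On that view 28 is a sound repeated-measures result whose settings were lost when the article was condensed. Much of this stands. The three-measurement design fits the 28 exactly, so the figure is probably not an arithmetic slip. The article also does not say outright that wp.kanova, alpha 0.05 and power 0.80 govern the secondary sentence; that is the natural reading, but it is an inference.

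The reply does not rescue the sentence. The repeated-measures route needs a correlation the article never gives, and it turns the half-SD effect presented as conservative into one of about 1.0 to 1.06 SD.

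Three stronger readings are tempting and not supported:

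- **That the trial must enrol 128.** That is the requirement under the named between-subject method. With repeated measures and a correlation near 0.9, 26 to 28 would do. Without a stated correlation, adequacy is undetermined rather than disproved.
- **That a null sprint-time result would be falsely called well powered.** Outcome measures & statistical analysis only summarises sprint performance descriptively, against percentage thresholds. Mixed models are named for the kinematic and force-velocity variables, so the consequence lies mainly with the tested secondary outcomes.
- **That the detectable difference can be quoted as one percentage of sprint time.** This needs the SD behind d = 0.87, and the article does not say whether it is a raw or a change-score SD.

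**Conclusion.** The secondary sample size is wrong as written. Under the one method named, and assuming alpha and power carry over, f = 0.25 needs 128 or 158 in total against the stated 28, where power is about 0.17 to 0.25. The calculation that does return 28 is undescribed and targets an effect about twice the stated one. For 0.5 raw SD, 28 is adequate only at a correlation of about 0.9.

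The repeated-measures figures assume equal variances, a common correlation between sessions and a difference present at one follow-up; they do not model muscle region. The primary requirement of 11 per group reproduces and is unaffected, and enrolment of 32 exceeds it.

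**What to change.** Keep N = 32 and rewrite the secondary-aim sentence:

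1. State the function used, the numerator df, the number of measurements, the assumed within-person correlation, alpha and power, and which effect f = 0.25 describes.
2. Give the detectable difference with 14 completers per arm: 1.10 SD of the change score, or about 1.10, 0.70 or 0.49 raw SD at correlation 0.5, 0.8 or 0.9.
3. Do not present 28 as giving 80% power for d = 0.5 unless a stated and justified correlation supports it.
4. Do not convert the detectable difference to a single percentage of sprint time.

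The cost is the wording of one paragraph. No participants are added and the primary analysis does not change. The drawback is that the stated sensitivity for the secondary aims becomes less favourable.
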